## Abstract

**Background:**

It is widely acknowledged that health policy and practice do not always reflect current research evidence. Whether knowledge transfer from research to practice is more successful when specific implementation approaches are used remains unclear. A model to assist engagement of allied health managers and clinicians with research implementation could involve disseminating evidence-based policy recommendations, along with the use of knowledge brokers. We developed such a model to aid decision-making for the provision of weekend allied health services. This protocol outlines the design and methods for a multi-centre cluster randomised controlled trial to evaluate the success of research implementation strategies to promote evidence-informed weekend allied health resource allocation decisions, especially in hospital managers.

**Methods:**

This multi-centre study will be a three-group parallel cluster randomised controlled trial. Allied health managers from Australian and New Zealand hospitals will be randomised to receive either (1) an evidence-based policy recommendation document to guide weekend allied health resource allocation decisions, (2) the same policy recommendation document with support from a knowledge broker to help implement weekend allied health policy recommendations, or (3) a usual practice control group. The primary outcome will be alignment of weekend allied health service provision with policy recommendations. This will be measured by the number of allied health service events (occasions of service) occurring on weekends as a proportion of total allied health service events for the relevant hospital wards at baseline and 12-month follow-up.

**Discussion:**

Evidence-based policy recommendation documents communicate key research findings in an accessible format. This comparatively low-cost research implementation strategy could be combined with using a knowledge broker to work collaboratively with decision-makers to promote knowledge transfer. The results will assist managers to make decisions on resource allocation, based on evidence. More generally, the findings will inform the development of an allied health model for translating research into practice.

**Trial registration:**

This trial is registered with the Australian New Zealand Clinical Trials Registry (ANZCTR) (ACTRN12618000029291). Universal Trial Number (UTN): U1111-1205-2621.

**Electronic supplementary material:**

The online version of this article (10.1186/s13012-018-0752-7) contains supplementary material, which is available to authorized users.

## Background

### Background and rationale

One of the challenges of evidence-based healthcare worldwide is to effectively and efficiently translate the findings of research into practice. Patient outcomes, patient satisfaction, cost-effectiveness, and quality outcomes benefit from evidence-informed decision-making [1–3]. Local healthcare policies that foster the timely translation of research findings to behaviour change can facilitate evidence-based practice [4–7]. In some cases, allied health policy and practice do not directly reflect current research evidence [8–12]. The delay in the translation of research into practice has also been documented for the medical [13] and nursing [14] professions, where it can take over 10 years for new scientific discoveries to enter day to day clinical practice [15, 16].

Allied health professionals generally have positive attitudes towards evidence-informed decision-making [8–10, 17–19]. Research receptivity and capability among allied health professionals are also influenced by organisational characteristics such as team dynamics, a culture of acceptance or resistance to change, and managerial support [20–22]. Allied health policy-makers and managers can influence these organisational factors and facilitate the translation of research into policy and practice [23]. However, they do not always have the training or access to knowledge transfer resources to assist them to engage effectively with research implementation [24, 25].

Implementation research has sought to develop strategies to reduce the gap between scientific evidence and practice [26]. A recently published systematic review identified 32 studies examining a number of different research implementation strategies for allied health professionals [27]. Education as a single strategy was most frequently evaluated, yet was not always successful in facilitating desired behaviour change [27]. Isolated educational strategies targeting individual professionals may not always meet the needs of complex organisational structures and multiple levels of decision-making involved in adopting an innovation. Providing resources to assist evidence-informed healthcare policy and management decisions may also facilitate behaviour change [28]. Slade et al. [3] highlighted the importance of allied health managers in fostering a research culture to embed evidence-based practice.

Developing evidence-based policy recommendations for allied health decision-makers has the potential to increase engagement with research implementation [29]. Short documents, which communicate key research findings in an accessible format, are one of the few research implementation strategies evaluated for use by resource allocation decision-makers, such as allied health managers [3, 23, 30, 31]. Single research implementation strategies have been reported as less successful than multifaceted approaches in some settings [32].

More interactive strategies may complement the provision of evidence-based policy recommendations, particularly in health services without a strong research culture [33]. One such interactive strategy is the use of knowledge brokers to work collaboratively with stakeholders, promoting the transfer and exchange of information [34]. Indeed, in Canada, many public health organisations have adopted knowledge broker roles as linking agents and capacity builders [35]. This is despite limited evidence to support their benefits [36]. Further high quality empirical research is needed to evaluate this particular implementation resource that could be provided to allied health policy-makers and managers to support the translation of research into practice.

### Implementation context

One area of allied health policy and practice that could better align with the current research evidence is the provision of allied health services to hospital wards during weekends. Routinely throughout the world, allied health services including physiotherapy, speech and language therapy, occupational therapy, social work, nutrition and dietetics, and podiatry, are delivered Monday to Friday. In some parts of the world, allied health services are also provided on Saturdays and Sundays [37–40]. Saturday physiotherapy services are the most common form of allied health provided outside business hours internationally [39, 41]. Only 30% of sub-acute hospitals provide weekend physiotherapy, despite evidence suggesting the provision of after-hours or weekend rehabilitation improves outcomes in the sub-acute rehabilitation setting [41–43]. Research implementation strategies could inform weekend allied health resource allocation decisions to better align policy and practice with contemporary research evidence.

### Objectives

This protocol outlines the design and methods for a multi-centre cluster randomised controlled trial to evaluate the success of select research implementation strategies for promoting evidence-informed weekend allied health resource allocation decisions by hospital managers. The implementation strategies will guide allied health managers in deciding how resources for provision of allied health services on weekends can be allocated between general medical and surgical, and sub-acute rehabilitation wards.

The resource allocation decision will be based on the following question: “How should resources for the provision of allied health services on weekends be allocated between general acute medical/surgical and sub-acute rehabilitation wards?”

## Methods

### Trial design

This multi-centre study will be evaluated using a three-group matched (based on health service regional status) parallel cluster randomised controlled trial. A three-group design will allow the comparison of two different research implementation strategies with a control. Stratification will be based on self-reported health service geographical classification as metropolitan or regional (including rural and remote), and clustering will occur at the level of weekend allied health resource allocation decision-making within each health service (e.g. health service level or hospital level).

This evaluation will be based on the Kirkpatrick Evaluation Model Hierarchy framework, which has four outcome levels that are designed as a sequence of ways to evaluate training programs [44, 45]. This study will focus on behaviour change outcomes in the third category.

### Study setting

The study sample will be drawn from Australian and New Zealand hospitals. Public or private, acute and sub-acute hospitals providing inpatient allied health services will be eligible for inclusion, with a representation of hospitals from both metropolitan and regional geographic classifications sought. Specialist hospitals such as maternity hospitals, paediatric hospitals, cancer centres, mental health and palliative care hospitals will be excluded. These hospitals will be excluded as no research regarding weekend allied health provision has been identified in these settings.

### Eligibility criteria

Allied health managers responsible for weekend allied health resource allocation decisions will be eligible for inclusion. All allied health professions currently providing an inpatient service to acute general medical and surgical wards, and sub-acute rehabilitation wards are eligible. A representation of the different allied health professions (e.g. physiotherapy, occupational therapy, speech pathology, dietetics, podiatry, psychology, exercise physiology, and social work) will be sought. We shall include those who currently provide weekend allied health services as well as those who do not currently provide services, but could potentially introduce these services.

### Interventions

Three intervention groups will be compared: control strategy group, implementation strategy group 1, and implementation strategy group 2. A summary of the intervention conditions described according to the Template for Intervention Description and Replication (TIDieR) guidelines is provided in Table 1 [46]. The two research implementation strategies were designed according to factors perceived to be associated with effective strategies and the inter-relationship between these factors to establish an imperative for change, build trust, develop a shared vision, and action a change mechanism, supported by effective employment of communication strategies and provision of resources to support change [23].

**Table 1 Tab1:** Intervention conditions according to the TIDieR guidelines

TIDieR criteria	Control group	Implementation strategy group 1	Implementation strategy group 2
Item 1. “Brief name: provide the name of a phrase that describes the intervention”	Usual practice control group	Evidence-based policy recommendation document	Evidence-based policy recommendation document and a knowledge broker
Item 2. “Why: describe any rationale, theory, or goal of the elements essential to the intervention”	Usual practice is the model of weekend allied health resource allocation decision-making at the research location. This serves as a pragmatic reference standard for implementation research	The evidence-based policy recommendation document will communicate research findings in an accessible format to facilitate evidence informed decision making [43]. This will be achieved by embedding an understanding of the political context within design, providing quality evidence communicated through a credible messenger, and fostering active engagement and linkages between policy-makers and researchers [44].	The evidence-based policy recommendation document will be the same as that provided to implementation strategy group 1. In addition, the knowledge broker will act as an intermediary agent to facilitate the transfer and exchange of relevant information between researchers and healthcare decision-makers to promote evidence informed decision-making [48, 49]. The knowledge broker will undertake activities focused on identifying and engaging with decision-makers, facilitating collaboration, identifying and obtaining relevant information, facilitating development of analytic and interpretive skills, creating research implementation resources, project coordination, communication and information sharing, network development, evaluating change, and supporting sustainability [48].
Item 3. “What (materials): Describe any physical or informational materials used in the intervention, including those provided to participants or used in intervention delivery or in training of intervention providers. Provide information on where the materials can be accessed (e.g. online appendix, URL).”	There will be no materials provided to the control group during the study period. Participants will be able to use materials ordinarily available for resource allocation decisions at their discretion.	The evidence-based policy recommendation document provided will be constructed in a simple 1:3:25 format developed by the Canadian Health Services Research Foundation [55]. It allows for a one-page outline of key messages, a three-page executive summary, and 25 pages presenting the report findings and methodology.	Participants will be provided with the same evidence-based policy recommendation document as implementation strategy group 1. Participants in implementation strategy group 2 will also be provided with access to a knowledge broker who may deliver educational materials including plain English summaries, slides, and handouts. Scientific abstracts and full-text journal articles relevant to the weekend allied health resource allocation decision may also be provided as applicable.
Item 4. “What (procedures): Describe each of the procedures, activities, and/or processes used in the intervention, including any enabling or support activities.”	Weekend allied health resource allocation decisions will follow usual practice conditions according to pre-existing individual and organisational processes.	The evidence-based policy recommendation document will be emailed to participants after random group allocation. This document was developed by project investigators through a consensus building approach and reviewed by a key stakeholder committee comprised of health professionals, managers, consumers, carer representatives, policy-makers, and academics.	The same version of the evidence-based policy recommendation document provided to implementation strategy group 1 will be emailed to participants after random group allocation. The knowledge broker will offer an initial consultation to perform an individual, organisational, and external environment (e.g. government policy) needs assessment, and develop a 12-month plan. One webinar session will be offered within the first 6 months depending on allied health manager availability, and monthly follow-up contact will also be offered.
Item 5. “Who: For each category of intervention provider (e.g. psychologist, nursing assistant), describe their expertise, background and any specific training given.”	Participants may consult a variety of individuals at their discretion.	A team of tertiary qualified academics, clinicians, and policy-makers from healthcare and business management backgrounds in Victoria, Australia produced and endorsed the evidence-based policy recommendation document.	A team of tertiary qualified academics, clinicians, and policy-makers from healthcare and business management backgrounds in Victoria, Australia produced and endorsed the evidence-based policy recommendation document. In addition, one knowledge broker with a PhD level qualification, from an allied health professional background, with research experience, currently employed as a post-doctoral research fellow will be recruited for this implementation strategy.
Item 6. “How: Describe the modes of delivery (e.g. face-to-face or by some other mechanism, such as internet or telephone) of the intervention and whether it was provided individually or in a group.”	Usual practice conditions may involve participants accessing information via internet, telephone, or face to face when making resource allocation decisions.	An electronic evidence-based policy recommendation document will be provided via email.	An electronic evidence-based policy recommendation document will be provided via email. The 1:1 initial knowledge broker consultation will be offered via telephone, videoconference, or face to face (where available) as per participant preference. The group-based webinar session will be offered via video or audio and follow-up contact will be offered via email or telephone (as per participant preference).
Item 7. “Where: Describe the type(s) of location(s) where the intervention occurred, including any necessary infrastructure or relevant features.”	Usual practice conditions are likely to involve participants making decisions at their place of work.	An electronic version of the evidence-based policy recommendation document will be delivered via email. Therefore, participants may be able to access at the location of their choice. This is most likely to be accessed at their place of work, in an acute or sub-acute hospital.	An electronic version of the evidence-based policy recommendation document will be delivered via email. Therefore, participants may be able to access at the location of their choice. This is most likely to be accessed at their place of work, in an acute or sub-acute hospital. The knowledge broker contact will occur via webinar, telephone, or email. Therefore, participants may be able to access at the location of their choice. This is most likely to be accessed at their place of work in an acute or sub-acute hospital. If the initial consultation can be arranged face to face, this will occur at a location convenient to both the participant and the knowledge broker, most likely at the participant’s place of work.
Item 8. “When and How Much: Describe the number of times the intervention was delivered and over what period of time including the number of sessions, their schedule, and their duration, intensity or dose.”	12-month wait list of usual practice conditions. The evidence-based policy recommendation document will be provided upon study completion.	One evidence based policy recommendation document will be provided to participants after random group allocation for the duration for the 12-month intervention period.	One evidence-based policy recommendation document will be provided to participants after random group allocation for the duration for the 12-month intervention period. The knowledge broker will provide one 60-min initial consultation, one 60-min group webinar, and one follow-up contact each month for the 12-month intervention period.
Item 9. “Tailoring: If the intervention was planned to be personalised, titrated or adapted, then describe what, why, when, and how.”	Usual practice conditions allow participants to take various approaches when making resource allocation decisions. These can be altered at participant discretion as per organisation policy and practice.	There is no adaptation planned for the evidence-based policy recommendation document during the study period.	There is no adaptation planned for the evidence-based policy recommendation document during the study period. The knowledge broker role is iterative in nature. Interaction will be tailored to the needs of the participants at the discretion of the knowledge broker based on their professional judgement.
Item 10. “Modifications: If the intervention was modified during the course of the study, describe the changes (what, why, when, and how).”	Not applicable for protocol	Not applicable for protocol	Not applicable for protocol
Item 11. “How Well (planned): If intervention adherence or fidelity was assessed, describe how and by whom, and if any strategies were used to maintain or improve fidelity, describe them.”	Adherence or fidelity will not be assessed in the usual practice control group, as no implementation strategy will be provided during the study period.	Whether or not participants read the evidence-based policy recommendation document will be explored in the 12-month follow-up qualitative interviews.	Whether or not participants read the evidence-based policy recommendation document will be explored in the 12-month follow-up qualitative interviews. Adherence to the knowledge broker component of the implementation strategy group 2 intervention will be monitored via the knowledge broker diary kept for the 12-month period.
Item 12. “How Well (actual): If intervention adherence or fidelity was assessed, describe the extent to which the intervention was delivered as planned.”	Not applicable for protocol	Not applicable for protocol	Not applicable for protocol

#### Control strategy group

The control strategy group will involve a 12-month wait-list for the provision of an evidence-based policy recommendation document at trial completion. This group will involve usual practice conditions, as per each health services usual decision-making process.

#### Implementation strategy group 1: provision of an evidence-based policy recommendation document

Participants will be provided with an electronic evidence-based policy recommendation document via email after random group allocation. This will have specific recommendations as to how the proportion of total allied health services should be delivered during weekends to align with current research evidence. Project investigators will develop draft recommendations through a consensus building approach based on the results of a systematic review and meta-analysis of the effectiveness and cost-effectiveness of in-patient weekend allied health services for improving patient and health service outcomes. In addition, a key stakeholder committee comprised of health professionals, managers, consumers, carer representatives, policy-makers, and academics will review draft recommendations and provide feedback before document finalisation. The document will be constructed in a simple format based on the Canadian Health Services Research Foundation [47]. This format allows for a one-page outline of key messages that have come from the research, a three-page executive summary, and 25-pages presenting the report findings and methodology.

### Outcomes

#### Primary outcome: alignment of weekend allied health service provision with policy recommendations at 12-month follow-up

Allied health service events (occasions of service) occurring during weekends, as a proportion of total allied health service events for the relevant hospital wards over a 1 month period will be used to determine alignment with the policy recommendation. This information will be collected at baseline for the preceding calendar month and the same corresponding calendar month at the 12-month follow-up. Allied health service events will be defined as per the 2017 National Allied Health Data Working Group (NAHDWG) endorsed National Allied Health Best Practice Data Sets (Additional file 1). Where data relating to allied health service events during weekends and weekdays is not available, data relating to allied health staffing levels or budgetary allocations during the weekend as a proportion of total allied health staffing levels or budgetary allocations for the relevant wards at each hospital for the preceding month will be used. Each participant cluster (hospital/health service) will receive a single classification as either (1) practice fully aligned with policy recommendation for both acute and sub-acute hospital wards, (2) practice partially aligned with policy recommendations (e.g. if practice on acute wards is completely aligned with the policy recommendation but not on sub-acute wards, and vice versa), or (3) practice not aligned with policy recommendation.

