### Data collection

Project investigators will collect the primary outcome data by requesting an allied health activity statistics report for the relevant wards at each hospital from the weekend allied health decision-maker/s at each health service. It will be requested that this report contains the minimum variables: number of allied health service events, date of each allied health service event, as well as hospital and ward location of each allied health service event. Where these data are not available, allied health staffing levels or budgetary allocations during weekdays and weekends for the relevant wards at each hospital in the preceding month will be requested. The mean hospital length of stay for relevant wards will be collected as reported by the hospital electronic patient management systems. Previous research has shown this data collection method for hospital length of stay provides completeness of data capture when compared to other methods [49]. Allied health managers will be encouraged to record the amount of time (person-hours) taken and other resources used (e.g. librarian) to make the resource allocation decision in a log. For implementation strategy group 2, these data will be combined with knowledge broker records of the amount of time attributed to each participant during the intervention period. Project investigators will perform audio-recorded semi-structured interviews either face to face, via telephone, or videoconference as per participant preference. Qualitative data from knowledge broker conversations will be audio-recorded, and regular communication (e.g. email, phone, online forums) with the knowledge broker will be captured.

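### The primary outcome is a weekend share within one calendar month with no adjustment for how many weekend days the month holds, which adds avoidable noise to the alignment category

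*Protocol article*

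**What the plan says.** The Primary outcome section of the protocol article takes weekend events "as a proportion of total allied health service events for the relevant hospital wards over a 1 month period will be used to determine alignment". The windows are stated: "This information will be collected at baseline for the preceding calendar month and the same corresponding calendar month at the 12-month follow-up". The share is then reduced to one ordinal value: "Each participant cluster (hospital/health service) will receive a single classification as either" fully, partially or not aligned. Full alignment needs both acute and sub-acute wards to comply.

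The section on implementation strategy group 1 says the policy document gives "specific recommendations as to how the proportion of total allied health services should be delivered during weekends", so the yardstick is itself a proportion. Its numerical value is not in the article.

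Where event data are missing, the weekend share of staffing or budget "for the relevant wards at each hospital for the preceding month will be used". The fallback is therefore month-based too. The Data collection section asks each site for the "number of allied health service events, date of each allied health service event" and the hospital and ward of each event.

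Nothing in the article standardises for the number of weekend days, uses whole weeks or sets a tolerance.

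**The concern.** Using the same calendar month at both time points controls for season. It does not control for how many Saturdays and Sundays the month contains. Weekend events divided by all events depends directly on that count, so an unchanged service can record a different share at baseline and follow-up.

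The same applies between sites. The Assignment section describes sites being recruited one after another, so follow-up months can differ. Identical services may then be compared with the same recommendation over 8, 9 or 10 weekend days.

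At stake is the precision of a three-level outcome with 25 analysed clusters per group, where one misclassified cluster is 1/25 = 4% of an arm. The Analysis section also tests alignment at ward level, and the economic evaluation counts clusters and wards that completely align, so the same noise enters there.

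**Working it through.** **The plan's own figure.** The article gives no figure for calendar variation. Its sample size reproduces: 25 per group at 50% versus 10%, with two-sided alpha 0.05 assumed, has exact Fisher power 0.833. That figure is not in dispute here.

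**Inputs.** The share and windows come from the Primary outcome section. Day counts come from the calendar. Weekend-day volume relative to a weekday, *r*, is not in the documents; I take 0.5 and show the range up to 1. The years 2018 to 2020 are an assumption based on the 2018 registration number.

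**Formula.** With *W* weekend days on which the service runs and *D* weekdays, share = rW / (rW + D).

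**Weekend days per month.** Months of 30 or 31 days hold 8, 9 or 10. February holds 8, or 8 to 9 in a leap year. Over a 400-year calendar cycle the count differs between the same month in consecutive years in 2765 of 4800 pairs (58%). It differs by two days in 301 of 4800 (6.3%), always with a 29 February between the windows. From 2018 to 2019 no month changes by two.

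**Service on both weekend days, no leap day between windows.** The count changes by at most one. For a 30-day month going from 8 to 9 weekend days:
- r = 1: 8/30 = 26.7% to 9/30 = 30.0%, +12.5%
- r = 0.5: 4/26 = 15.4% to 4.5/25.5 = 17.6%, +14.7%
- r = 0.25: 2/24 = 8.3% to 2.25/23.25 = 9.7%, +16.1%
- r towards 0: limit (9/21)/(8/22) = 1.179, +18%

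**Saturday-only service, r = 0.5, 2018 to 2019.** The number of Saturdays changes in 4 of 12 months:
- August: 2/25 = 8.0% to 2.5/24.5 = 10.2%, +28%
- September: 2.5/22.5 = 11.1% to 2/23 = 8.7%, -22%
- November: 2/24 = 8.3% to 2.5/23.5 = 10.6%, +28%
- December: 2.5/23.5 = 10.6% to 2/24 = 8.3%, -22%

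In the other eight months the shift is at most about 4%. Over the 400-year cycle the Saturday count changes in 1590 of 4800 pairs (33%). Among pairs with equal month length and no intervening leap day it changes in 953 of 3539 (27%). This case matters because the Implementation context section states: "Saturday physiotherapy services are the most common form of allied health provided outside business hours internationally".

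**With a 29 February between the windows, r = 0.5.** May 2019 to May 2020 goes from 8 to 10 weekend days. A both-days service moves from 4/27 = 14.8% to 5/26 = 19.2% (+30%). A Saturday-only service moves from 2/25 = 8.0% to 2.5/23.5 = 10.6% (+33%).

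**Between sites in one year.** No leap day is needed. Identical both-days services measured in May 2019 (8 weekend days, 23 weekdays) and June 2019 (10 and 20) record 4/27 = 14.8% and 5/25 = 20.0%.

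**After the fix.** Any 28 consecutive days contain each day of the week four times, so 20 weekdays and 8 weekend days. An unchanged service then gives the same share every time: at r = 0.5, 4/24 = 16.7% for both days and 2/22 = 9.1% for Saturday only.

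**The case against.** Five points can be made for leaving the plan alone.

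- **The large swings are not routine.** This stands. A reader might infer that the same site commonly moves by about a third. At 12-month spacing, a both-days service does so only across a 29 February, and even a Saturday-only service stays below that in ordinary years. The 58% of month pairs with some change must not be read together with the largest shift.
- **A category change needs a site near the cut-off.** This stands. The article does not say whether the recommendation is a minimum, a range or another form. A site with no weekend service scores 0% under any calendar, and the sample size section anticipates large changes in alignment.
- **Randomisation protects the comparison.** This stands. Allocation uses blocks of three, six or nine within strata, so calendar effects are equal between arms in expectation. A reader might infer bias between arms; the documents do not support that.
- **Day-count standardisation may be left to an analysis plan.** This stands only in part. Such a plan may exist, but the article itself fixes the calendar month as the window for the primary outcome, and anyone following it as written gets the noise.
- **Whole Monday-to-Sunday weeks would be awkward.** This is correct. Four such weeks fit inside only 2355 of 4800 months (49%), so the remedy should not depend on them.

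**Conclusion.** The point holds as a modest, avoidable loss of precision in the primary outcome. At r = 0.5 without an intervening leap day, an unchanged both-days service shifts by 0 to about 15% relative (at most about 18% for any r). That is about 2 percentage points at r = 0.5 and about 3 at r = 1. An unchanged Saturday-only service shifts by about -22% to +28% when its Saturday count changes, and by about 4% or less when it does not. Two-day changes in the weekend count affect about 6% of month pairs.

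These sizes rest on an assumed weekend-to-weekday volume and on constant activity per day. The direction does not depend on either. The noise is non-differential. How many clusters would change category, and how much power is lost, cannot be derived from the article because the cut-off is not given. The finding does not invalidate the trial or its sample size.

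**What to change.** Keep the same calendar month at baseline and follow-up, but compute the share over a fixed 28 consecutive days inside it, for example days 1 to 28. This always fits within the month and needs only a date filter on the report already requested.

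An alternative that keeps every day is a day-standardised share. Where Saturday and Sunday volumes are equal, this is 2 × mean weekend-day events / (5 × mean weekday events + 2 × mean weekend-day events). Over the 28 days it equals the simple share. Over a whole month, Saturday and Sunday means should be taken separately and added, because pooling does not fully correct a Saturday-only service. With r = 0.5, 4 Saturdays and 4 Sundays give 0.5/5.5 = 9.1%, but 5 and 4 give 0.556/5.556 = 10.0%.

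For the fallback, apply the same 28 days to staffing rosters. Where only monthly totals or budgets exist, divide them by the number of weekdays, Saturdays and Sundays that they cover before forming the share.

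The cost is one or two sentences in the outcome definition. From 0 to 3 days of events per month go unused, and sites supplying only monthly totals need the day-count scaling.
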